## Abstract

Psychotherapy is one of the evidence-based clinical interventions for the treatment of depression in older adults with dementia. Randomised controlled trials are often the first methodological choice to gain evidence, yet they are not applicable to a wide range of humanistic psychotherapies. Amongst all, the efficacy of the Gestalt therapy (GT) is under-investigated. The purpose of this paper is to present a research protocol, aiming to assess the effects of a GT-based intervention on people with dementia (PWD) and indirect influence on their family carers. The study implements the single-case experimental design with time series analysis that will be carried out in Italy and Mexico. Six people in each country, who received a diagnosis of dementia and present depressive symptoms, will be recruited. Eight or more GT sessions will be provided, whose fidelity will be assessed by the GT fidelity scale. Quantitative outcome measures are foreseen for monitoring participants’ depression, anxiety, quality of life, loneliness, carers’ burden, and the caregiving dyad mutuality at baseline and follow-up. The advantages and limitations of the research design are considered. If GT will effectively result in the treatment of depression in PWD, it could enrich the range of evidence-based interventions provided by healthcare services.

## 1. Introduction

Dementia is a global epidemic; it is estimated that there are over 55 million people living with dementia worldwide, with the number expected to almost triple by 2050. Most of this increase can be attributed to population ageing, which is occurring at an unprecedented rate in low- and, particularly, middle-income countries [1].

Dementia, also called major neurocognitive disorder, is an umbrella term that describes a set of symptoms of cognitive, psychological, and behavioral nature that compromise the daily functioning of a person, the underlying cause of which may be one or more neurocognitive diseases, of which Alzheimer’s disease (AD) is the most common. Dementia can affect people at any age, but its prevalence increases significantly over time, particularly after the age of 65, doublings every five years [2].

There is a correlation between ageing, dementia, and depression. Depression predominantly affects older people, with the prevalence increasing to 9.3% in over 60 s [3]. Changes related to age and chronic physical diseases may contribute to modifications in the brain areas involved in the regulation of mood, i.e., the frontostriatal circuits, amygdala, and hippocampus, respectively, predisposing to depression [4]. Moreover, isolation, relocation, caregiving, and other age-related psychosocial stressors are a significant risk factor for depression in later life [5]. Chronic stress can increase cortisol levels, which contribute to depressive disorders and the atrophy of the hippocampus, also affecting its cognitive functions [6,7,8].

Literature shows that the association between depression and dementia is complex and bidirectional. Longitudinal studies suggest that recurrent depressive symptoms in adulthood, late-life depression, and chronic subsyndromal depression significantly increase the risk of dementia over time [9,10,11]. Therefore, early-life depression may be considered a risk factor for dementia in older age, and late-life depression may be a prodrome to dementia. Likewise, dementia can be considered a risk factor for depression. People with dementia (PWD) have a higher rate of overt depression, i.e., 20% in AD, 37% in frontotemportal dementia, and 50% in vascular dementia [12,13,14], whilst depressive symptoms have been reported in 30–50% of AD patients [15].

Depression in dementia can be underdiagnosed because its presentation in older people can differ from the Diagnostic and Statistical Manual of Mental Disorders (DSM)-5 [16] criteria, which are mostly based on adult populations, and the cognitive symptoms may overlap with the dysfunctional signs of dementia [17].

### 1.1. Dementia as a Social Disease: The Impact of Dementia on Informal Carers’ Health and Social Life

Dementia affects the person suffering from it, as well as all his/her family and social network. In fact, most PWD live at home assisted by their family members (e.g., spouses and children) who become their main carers [18].

Beyond the multiple cognitive impairment, the behavioural and psychological symptoms experienced by PWD, such as depression, personality changes, aggressiveness, delusions, hallucinations, wandering, and sleep disturbances [19,20], are challenging to accept and manage by informal carers. The latter, therefore, often tend to reduce the occasions on which they can be in public, in order to avoid embarrassing situations, thus leading them to social isolation, defined as the lack of social contact, relationships, and integration [21,22,23]. PWD are considered one of the most socially excluded groups of older people [24,25], and so are their informal carers [26], with a negative impact on their health-related quality of life [27]. The association between social isolation and dementia is bilateral because the former is both the consequence and one of the driving forces behind the latter. Empirical evidence greatly highlights the association between social isolation and dementia and vice versa [28]. Family carers of PWD subsequently report increased rates of caring strain, physical and mental health problems, and experience difficulties in maintaining employment, leisure activities, and family interactions, all of which has an impact on their quality of life [28]. Moreover, family carers can experience fatigue, frustration, a sense of inadequacy, feelings of being trapped, and loneliness, with the latter worsened by social exclusion and stigma characterising the care recipients. Furthermore, increased caregiver burden, in relation to behavioural or depressive symptoms in dementia, has been shown to lead to neglect or physical and psychological abuse by the family carer [29,30]. With the advent of the COVID-19 pandemic, older people, including PWD, have been called to shelter because they have been identified as being at high risk of contracting the SARS-CoV-2 infection [31], and the rules around social distancing have restricted access to community services for PWD and their carers. During the outbreak, few care services have adapted to providing remote support to PWD [32], and most centres for cognitive disorders and dementia markedly reduced their activities. As a consequence, many PWD experienced faster symptom deterioration during the pandemic [33]. Social isolation caused a decline in memory function, increased anxiety and depression symptoms (especially in individuals with mild-to-moderate dementia), and worsened the general health condition of informal carers who experienced increased tiredness, feelings of being overwhelmed, health problems, sleep disturbances, and greater irritability associated with social isolation [34]. A clear association has been found between the cognitive decline of older PWD during the lockdown and increase of family carers’ psychological distress [35].

In light of the above, psychotherapy should involve the person in need, as well as the family carer, as an individual belonging to his/her environment, in order to put in place appropriate measures for treating dementia and correlated depressive symptoms. GT prioritising the relationship between the person (and his/her social contacts) and environment may be an effective approach for mitigating the disruptive impact of depression on PWD and family carers, as described in the paragraphs below.

### 1.2. The Contest of Dementia Diagnosis and Formal Care: A Snapshot of Italy and Mexico

The care and the management of dementia differs country-by-country, depending on epidemiological figures, the long-term care (LCT) system, welfare regimes, and level of country income. In Latin America, the prevalence of diagnosed dementia in 2010 was 3.10 million cases, compared to 9.95 million in Europe, and an increase of 393% is expected by 2050, compared to an 87% rise in Europe [36]. The increasing number of diagnosed PWD will contribute to growing inequalities in low- and middle-income countries, where 15% of dementia-related costs is covered by social care, compared to 40% in high-income countries [37].

Despite Europe being considered a wealthy continent with a better health system, compared to Latin America, the quality and level of care provided to PWD, from the time of diagnosis onwards, can differ significantly in each country.

This article shows an intervention research protocol, targeted to PWD and depressive symptoms living in Mexico and in Italy. Since these countries have different LTC systems and gross domestic products (GDP), the epidemiological and socio-economic contexts have been explored and are described in the following sub-paragraphs, in order to provide the rationale of the study protocol presented in this paper.

In Italy, the overall number of PWD will almost double from 2018 to 2050, reaching the figure of 2,247,715 individuals, which will represent 4.13% of the overall population, compared to 2.12% in 2018 [38,39], thus keeping in line with the European and western world trend. In the country, diagnosis of dementia is frequently made in hospital, when the person is at a middle-advanced stage of the illness, contrary to what happens in other European countries, such as the United Kingdom, where health services promote early diagnosis, and memory services have a great focus on providing support at the early stages of the disease. Although the intent is to slow down the progress of the disease, in Italy, there is neither a clear strategy to facilitate early diagnosis nor to promote a person-centred care aimed at keeping the person independent and cutting the cost of LTC. The diagnosis of dementia is often not even communicated to the patients, but only to their family members, and working on acceptance of the new condition can be problematic.

Once the diagnosis is received, families often attempt to keep the PWD at home and manage the care assistance by using support from both public and private sources. The National Health Service offers home healthcare services (Assistenza Domiciliare Integrata, ADI), which include specialist assistance from nurses, physiotherapists, and medical doctors; yet this is only for an average of 16 h per year, per patient, and does not include psychotherapy [40]. The last available data reported that only 9.5% of PWD received this type of support in 2016 [41]. At a local level, the municipality partially offers, through a voucher scheme, another type of home social care service (Servizio di Assistenza Domiciliare, SAD) that covers basic individual needs, e.g., food intake for highly dependent older people. The provision of SAD can vary significantly across Italian areas and is not well-integrated with the ADI [42]. Moreover, it is neither considered a sufficient nor appropriate service for covering the needs of PWD and their family carers [43]. Another type of dementia care voucher, which is not distributed evenly across the country, consists of funding to access a psycho-educational intervention in “Alzheimer Day Centers”, available only to 12.5% of families, despite this being part of an essential level of assistance [41]. Finally, the state care allowance (Indennità di Accompagnamento) is a universal and not means-tested monetary transfer of 522.10 EUR per month, provided to the person in need of care. Such a contribution often partially covers the cost of live-in (migrant) care workers who can guarantee H24 home assistance to PWD [41]. This means that families cover most of the cost of care with their own budget. [44].

Epidemiological figures in Mexico mirror Latin America’s trend, with a prediction of nearly 1.5 million cases by 2030 and increase of 414% between 2010 and 2050 [45]. Only in recent years has there been a governmental effort to boost the proposal of the first national Alzheimer’s Plan of Action (APA) [46]. The APA aims at promoting PWD and their families’ well-being by empowering services of the Mexican healthcare system and cooperating institutions. Guidelines and strategies for implementing specific actions have been published, the second strategy being “To ensure access to quality services” [46,47]. However, currently, many families in rural areas and living in poverty neither have access to specialised dementia centres nor training and guidance for home care assistance. Community-type care has emerged as a response and alternative. However, the aim of this type of support is limited to providing information to sensitise the community, and lacks an ethical approach, based on empirical research, prior to applying the intervention.

### 1.3. Psychological Support and Psychotherapy Interventions: Gestalt Therapy View on Dementia and on Depression

In light of the above, very little is offered, in terms of psychological support, for PWD and their families to hinder depression, both in Italy and in Mexico, as well as when PWD live at home and in residential or semi-residential institutions. Conversely, the treatment of depression is very important because depression affects the relationship between PWD and their family, as the person becomes more apathetic and less cooperative. As a result, it becomes even more difficult for family members to take care of the person with dementia, with negative effects on the health of the informal carer (and level of care required), social dimensions (i.e., social inclusion and participation), and, ultimately, progression of the disease. In fact, some studies have underlined the association of depression in dementia with decreased quality of life [48] and level of autonomy in performing the instrumental activities of daily living (IADL) [49], quicker progression of cognitive decline, earlier admission to residential facilities [50], and, as described above, a clear association to the interruption of social relationships [27]. In light of this, it is crucial to identify the symptoms of depression early in people with dementia and offer them appropriate psychotherapeutic support.

Gestalt therapy (GT) is a phenomenological, aesthetic, and field-oriented approach based on humanistic and holistic principles. GT theory considers that, through human development, individuals learn ways of coping and relating to others in their family environment, the learning of which becomes then generalised and automatic, inscribed in the procedural memory that tends to be economically fast for our brain and kept out of awareness [51]. The primary aim of GT is to restore the wholeness of the experience of the person, including bodily feelings, movements, emotions, and the ability to creatively adjust to environmental conditions by empowering the awareness in the present moment. The therapist works to address the implicit knowledge of patients by accessing her/his non-verbal and creative resilience. The *phenomenological* principle addresses the experience of the client in its wholeness by paying attention to nonverbal cues over the cognitive ones. For instance, rather than focusing on the memory of an event, the emphasis is on developing the ability to stay in the therapeutic relationship harmonically, like in a dance, and to learn how to express their own wish for relational contact and sense of agency. The *aesthetic* principle allows therapists to look at the client’s experience through all human senses; instead of using cognitive criteria to evaluate the capacity for relational contact of the client, the therapist can consider other resilient aspects, such as their body movements, emotions, level of arousal, and direction of energy (intentionality for contact) [52]. The *field* principle allows the therapist to work with reciprocity and consider synchronicity as a cue to evaluate the ability of the client [53]. An effective intervention has to be focused on the relational “dance” that therapist and client co-create, more than on achieving a certain individual goal. Whilst a goal is agreed upon at the time of the therapy contract, the focus of the work will not be on the goal, which will only be discussed at review points and the end of therapy. The “dance of reciprocity” will also enable the client to fulfil cognitive goals because this relational “dance” will support their ability to cope and adjust to the environment [52]. In this way, the intervention will be on the function of the client to flexibly adapt to their environment, in different and creative ways, rather than on acquiring certain behavioural aims.

Because of Gestalt therapy’s experiential and experimental nature, there is a lack of empirical research supporting its evidence. A recent systematic review selected eleven scientific papers on the effectiveness of the approach, confirming the validity of GT as a clinical model [54]. In favour of the use of GT with PWD, it is possible to consider some neuropsychological and relational aspects of the approach, together with the common residual abilities of PWD. First of all, it is important to take into account that, although working memory, short-term memory, and language can become impaired with the progression of dementia, emotional and procedural memory are retained skills that may decay only at the very late stages of the disease [55]. GT focuses on procedural memory, or nondeclarative memory, which is related to embodied learning on how things are done, through the selection, use, retention, and recall of perceptual, cognitive, and motor skills [51]. This procedural level should be the priority in the therapeutic process when working with PWD and, in general, to promote a long-term change. Gestalt therapists work on attunement to movement, facial expressions, posture, tone of voice, the affective content of communication, and supporting difficult emotions that emerge in the relational field with the patient [56]. By focusing on the importance of the person’s adaptation to the new situation (neurological, emotional, and social), Gestalt therapists help the patient to create new responses to the changing environment, thus addressing the social dimension of the illness [54] by supporting resources, instead of being concerned with what does not work and continuous losses. The changing environment for PWD relates not only to the outside world, but also to their experience of self, in relation to the change and challenges that dementia brings, which adds a level of complexity when working with these patients.

Considering the aims of this study, it is also relevant to define depression in GT, which is viewed from a phenomenological and aesthetic perspective [57]. GT offers an original attempt to reformulate depression, in terms of the experience of “contact” with the environment. “Contact” in GT is the ability to interact with the environment with the aim to fulfil a need. GT connects depression with five dimensions, related to the organism/environment field, which have also been observed to co-occur in both the client and the therapist: (1) depression is considered the lack of connection with the environment; (2) a depressive experience is viewed as the renunciation of the desire to be desired, rather than related to the frustration of past desires not being fulfilled; (3) depression is seen as the inability to transcend oneself; (4) depression is conceptualised as a lack of hope, rather than a lack of happiness; (5) depression indicates the inability to feel oneself—from the bodily sensations level to the emotional one [58].

The effectiveness of GT for depression has been supported by a small number of studies, one of which involved geriatric patients with depression and anxiety [54,59]. In fact, despite the potential effectiveness of this approach, there is still a gap in research on using GT for PWD and those with depressive symptoms.

The experiential, creative, and flexible aspects of GT can provide a unique way of working therapeutically with PWD because of the focus on the non-verbal part of the experience, residual abilities of the person, and use of body movement and art as aims of communication, which can greatly facilitate the therapeutic engagement towards the attainment of therapeutic goals.

GT can offer a way of working with PWD and depression that can easily incorporate access to other forms of support and activities, not only in a talkative way, but in a practical one. The creative flexibility implicit in the approach allows therapist and patient to develop the therapeutic path together, which can be extended to the outside world, therefore going beyond the walls of the therapy room. For instance, they can agree that, as part of therapy, they attend a walking group or go for a bus trip together.

### 1.4. Selection of the Research Design: Single-Case Experimental Design

Scientific literature offers plenty of evidence that non-pharmacological interventions are the best choice for managing the psychological and behavioural symptoms of dementia, including depression [60,61]. Pharmacotherapy for depression in dementia has unclear outcomes, and antidepressants may accelerate the progression of dementia [62,63,64]. Psychological therapies, particularly cognitive behavioural therapy (CBT), are among the most evidenced approaches to treat depression in dementia [65].

In a systematic review, Cheston and Ivanecka [66] highlight that there is poor evidence of the efficacy of psychotherapy for the treatment of non-cognitive symptoms in dementia patients. The authors state that manualised interventions, such as CBT, are best evidenced because the treatment can be measured through the RCT model, yet RCTs have important limitations in psychotherapy research. The American Psychological Association [67] states that the single-case time series design can be as valid as RCTs. Moreover, single-case experimental designs (SCEDs) can ensure high-quality research for small heterogeneous groups in clinical settings, allowing for the focus on the unique needs of patients [68], rather than on a set of given techniques. It is well-known that dementia affects each person differently; therefore, it is crucial to adopt person-centred approaches in dementia care and tailor the psychotherapeutic treatment to the needs and presentation of each patient. Gestalt psychotherapy can be a flexible and user-centred approach that, for the reasons mentioned above, could be proved efficient in treating depression in dementia. Considering the qualities of GT introduced above, SCEDs appear to be the best type of investigation to measure the effectiveness of the Gestalt approach.

### 1.5. Proposed Research Aims and Objectives

The general objective of the research is to determine whether or not GT is an effective treatment for depression in PWD.

Specific objectives of the study are:-To assess if there is a pre/post improvement and, if so, how great this is (clinical significance), according to the outcome variables rates, as well as whether it can be attributed to the therapy intervention.-To assess if study participants suffer with loneliness.-To assess if loneliness is mitigated by the regular contact with the therapist.-To assess if the regular contact with the therapist affects the level of depression.-To assess if a clinical improvement of depression symptoms has an indirect effect on the level of family carers’ burden.-To assess if a clinical improvement has an indirect effect on the mutuality of the relationship between the patient and the family carer.

In order to achieve the objectives, the following research questions will need to be answered:Is there any pre/post treatment improvement?If the answer to question 1 is yes, is the change clinically significant (reduction of symptoms by 50%)?If loneliness is a factor, is the improvement solely due to the social contact with the therapist? ORCan the improvement be attributed to the therapy intervention?Can the improvement of the patient also have an impact on the caregiver’s burden and level of mutuality?

The researchers hypothesised that: depressive symptoms will improve post GT treatment and the improvement will be maintained at follow-up; the level of loneliness, if a factor, can decrease post-treatment and remain so at follow-up; the improvement of symptoms is related to the GT treatment; the level of burden of the family carer will reduce whilst the mutuality in the relationship will increase as the PWD’s depression improves.

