## 2. Materials and Methods

### 2.1. Research Design

The ABA single-case experimental design will be used for the purpose of the study, as explained previously.

The research method is divided into three phases: an “A” baseline period of two weeks between the assessment session “0” and initial psychotherapy session; a “B” intervention period of minimum eight GT sessions; an “A” follow-up period of six months after the end of the intervention, with measurements at the final session, after two weeks and six months. More specifically, in relation to data collection, the following will happen in each phase: A—at the baseline, outcome measures will be administered at session “0”, and individual target complaints (TC) will be recorded daily for the following two weeks; B—in the intervention phase, target complaints will be completed daily; A—in the follow-up phase, participants will continue with daily assessment for another two weeks, while outcome measures will be administered at the final session, i.e., week two and week twenty-four (Figure 1).

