The target complaints (TC) daily form [81] is a co-constructed self-report measure of three central idiosyncratic issues and one general wellbeing item. The items are identified together with the therapist at session “0”, then rated daily on a Likert-scale, from 1 to 10, where 1 equals “not bothered at all” and 10 equals “could not be worse”. Each complaint should be concrete, measurable/quantifiable, frequent, stable without treatment, relatively independent from one another, specific, and negatively formulated. The main instruction that helps identifying and scoring the target complaints is “Please record up to three presenting concerns that brought you to therapy. Circle the number that best represents your personal degree of discomfort as a result of each issue.” Improvement on global assessments and target complaints correlated at 0.71 [82], and test-retest reliability was at 0.76 [83].

The University of California, Los Angeles loneliness scale version 3 (UCLA-LS3) is a 20-item, self-reported questionnaire, broadly used to measure subjective feelings of loneliness and social isolation in various populations, including older adults and people with dementia. UCLA-LS3 has a well-established validity and reliability for its use in different languages, among which are Italian and Spanish [84,85,86]. The scale will be used to assess whether loneliness is a present factor and to observe whether regular contact with the therapist, rather than treatment, can influence this secondary variable and, thus, the level of depression (primary variable).

The quality of life-Alzheimer’s disease (QOL-AD) is a self-report tool for the PWD and their proxy/caregiver, based on 13 items of multiple domains, including physical health, mood, marriage, and fun. QOL-AD has excellent internal consistency and inter-rater reliability, as well as good criterion and construct validity [87].

The Ad-hoc common assessment tool is a questionnaire aimed at obtaining information on the level of care required by the PWD. It is an idiosyncratic and non-standardised tool, containing questions such as the weekly hours of caregiving and type of formal or informal support involved.

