### 2.5. Data Analysis

Continuous variables will be analysed and reported as mean ± SD (standard deviation) or median and IQR (interquartile range), on the basis of their distribution (assessed through Shapiro–Wilk test). Discrete variables will be reported as absolute frequencies and percentage.

In order to evaluate any pre/post improvements (from baseline to follow-up: at the final session, after two weeks and twenty-four weeks following the end of the treatment) in the main outcomes, i.e., depression and anxiety symptoms (GDS; NPI-A), quality of life (QOL-AD), and the therapy outcome (CORE–OM), three types of analysis will be carried out: (a) visual analysis, comparing the target complaint (TC) scores during the three phases; (b) mean difference from baseline to follow-up tested, by means of paired t-test or Mann–Whitney U test, according to the distribution of the outcome variable [99]; (c) mean baseline reduction (MBLR) for obtaining the effect size for single-case designs [100,101,102], as follows:MBLR = (Mean of Baseline phase − Mean of Follow-up phase) × 100/Mean of Baseline phase.(1)

The same procedure will be applied for the secondary outcome, i.e., loneliness. Additionally, data collected from family caregivers (i.e., QOL-AD family version, caregiver burden scale, and the mutuality scale) during the three phases of the study will be compared with subjects’ outcomes, in order to evaluate indirect effects of the treatment, by means of Pearson or Spearman correlation coefficients, as appropriate.

Blind raters will assess the fidelity of the approach by rating a small sample of sessions through the GTFS.

A two-tailed *p* value < 0.05 will be considered significant. Data will be analysed using SPSS for Windows V24.0 (SPSS Inc., Chicago, IL, USA) and Simulation Modeling Analysis (SMA) for Windows V07.30.20 (ClinicalResearcher, Jeff Borckardt, Medical University of South Carolina).

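### The contact-or-therapy question cannot be answered by this design, because regular therapist contact occurs only as Gestalt therapy sessions

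*Protocol article*

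**What the plan says.** Section 1.5 of the protocol article lists among its specific objectives whether regular contact with the therapist eases loneliness, and "To assess if the regular contact with the therapist affects the level of depression". Its research questions then set two explanations against each other: where loneliness plays a part, "is the improvement solely due to the social contact with the therapist", or can the improvement be attributed to the therapy? The first specific objective also asks whether improvement is attributable to the intervention.

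Section 2.4 ties this contrast to an instrument. The UCLA-LS3 is to be used "to observe whether regular contact with the therapist, rather than treatment, can influence this secondary variable and, thus, the level of depression", with depression named as the primary variable.

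On design, section 2.1 states: "The ABA single-case experimental design will be used for the purpose of the study". Phase B is an "intervention period of minimum eight GT sessions", which section 2.2 describes as individual sessions of one hour each week. UCLA-LS3 is taken at session 0, the final session, and weeks 2 and 24 of follow-up (section 2.4, Table 1). Section 2.5 says: "The same procedure will be applied for the secondary outcome, i.e., loneliness", meaning the pre/post procedure used for the main outcomes.

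The Discussion (section 3) says it will be possible to review whether changes are attributable to the Gestalt work. Section 4, on limitations, does not mention that contact and therapy cannot be separated.

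**The concern.** The research question asks for a choice between two causes that the design always applies together. A participant who starts GT starts weekly contact with a therapist, and one who stops GT stops that contact. Nobody receives one without the other on a regular basis.

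What is at stake is how the main result is read. If depression improves, the wording of sections 1.5 and 2.4 invites the authors to use the loneliness scores to say that the improvement was, or was not, only a matter of company. The data could support neither statement. A fall in UCLA-LS3 could come from contact, from GT itself (section 1.3 allows shared outings as part of therapy), or from the relief of depression.

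**Working it through.** The plan gives no figure on this point, so there is none to reproduce. The check is whether separate effects of contact and therapy can be estimated at all.

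**Inputs**
- Baseline A: two weeks, 14 daily ratings (section 2.1).
- Phase B: at least eight weekly sessions (sections 2.1 and 2.2), taken here as 8 × 7 = 56 days.
- Follow-up A with daily ratings: two weeks, 14 days (section 2.1).
- UCLA-LS3: four time points, none between session 0 and the final session.
- Therapist contact outside GT: the only instance described is session 0, where the target complaints are agreed (section 2.4).

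**Step 1: daily series.** Write the outcome on day t as a + b·C(t) + g·T(t), where C marks regular contact and T marks GT. Over 14 + 56 + 14 = 84 days, C and T are both 0 in the A phases and both 1 in phase B. The two columns are identical, so the matrix (intercept, C, T) has rank 2 of 3. Only b + g can be estimated.

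**Step 2: UCLA-LS3 time points.** With the minimum course, the cumulative count of regular contacts is 0, 8, 8, 8 and the cumulative count of GT sessions is 0, 8, 8, 8. The rank is again 2 of 3. A longer course raises both counts together, so pooling patients with different numbers of sessions does not help.

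**Step 3: session 0 as contact without GT.** Coding day 1 as contact gives C = 1 on 57 days and T = 1 on 56. The squared correlation is (56 × 27)/(57 × 28) = 1512/1596 = 0.947, so r = 0.973 and the variance inflation factor is 1/(1 − 0.947) ≈ 19. The rank is formally 3, but the separation rests on one baseline day, which is not regular contact.

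**Step 4: what would separate them.** Adding an assumed 56-day contact-only phase before phase B raises the rank to 3 of 3. A contact-only comparison group would serve the same purpose. More patients or more days of the present design would not.

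**Step 5: a loneliness–depression change correlation.** There are at most 12 pairs. After the stated dropout of 20–30%, 12 × 0.8 = 9.6 or 12 × 0.7 = 8.4 remain. Two-sided significance at 0.05 needs |r| of about 0.58 with 12 pairs and 0.71 with 8. Even a strong correlation would not show which change led to the other.

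**The case against.** **The data carry some indirect information.** If depression improved while loneliness did not change, a route through loneliness would be less plausible. Contact and GT both stop at the final session and the outcomes are repeated at weeks 2 and 24, so a benefit that lasted might argue against a pure effect of ongoing company. This stands. A reader might infer that every pattern of results is equally compatible with contact and with therapy, and that goes too far. The evidence is still weak: other non-specific effects of contact need not act through loneliness, and contact effects may outlast the contact.

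**The objectives do not state the contrast.** This also stands. The two objectives on regular contact ask only whether contact affects loneliness and depression. The opposition to therapy is explicit in the research question and in section 2.4. The objectives need rewording, not deletion.

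**Contact and therapy do not always coincide.** Session 0 is a therapist meeting without GT, so the statement is exact only for regular contact. Regular contact is what the objectives and section 2.4 name.

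**The wording is mild and the variable secondary.** Section 2.4 says observe, and no rule converts a UCLA-LS3 result into a verdict. The research question nevertheless offers two alternatives and asks which holds.

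**An analysis plan may deal with it.** It could supply a link between loneliness and depression scores, so the absence of that link from the article is not a fault. It could not supply a condition that the design lacks.

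**Conclusion.** The point holds. In the stated design regular therapist contact and GT are aliased across the phases, and only their combined effect is estimable. This is a matter of identification, not precision, so it does not depend on the sample size of 12, the dropout rate or the significance level. The day counts used above are illustrative, and the result is the same for any length of phase B.

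It rests on the design as described: weekly GT sessions are the only regular therapist contact, and there is no contact-only phase or comparator.

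The reach is limited. A reader might infer that the pre/post estimate for the geriatric depression scale is undermined. This point leaves that estimate unchanged. It limits what any change may be attributed to: at most GT sessions together with the contact they involve. The correction is worth making because the article poses the attribution as answerable and does not list the limit in section 4.

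**What to change.** - Section 1.5: remove the research question that sets contact against therapy. In the two objectives, replace regular contact with the therapist by GT sessions (including therapist contact). In the first objective, say that any attribution is to that package.
- Section 2.4: remove the phrase that has UCLA-LS3 distinguish contact from treatment.
- Section 2.5: report loneliness at session 0 and its change. Label any correlation between change in UCLA-LS3 and change in the depression scale as descriptive, with at most 12 pairs and no direction of effect.
- Sections 3 and 4: state that non-specific contact cannot be separated from GT, and qualify the Discussion's statement on attribution to match.

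This is wording plus, at most, one descriptive statistic. It adds no participant, visit or instrument, and its cost is one attribution claim. If the sponsor wants to keep the question, the design needs a contact-only phase or comparison group, with the extra time or participants that this entails.
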